## Methods/design

### Overview

The non-alcoholic fatty liver disease: implementing the right care in the right place at the right time (NAFLD-RRR) study is a quasi-experimental study with a prospective intervention and historical control group. The intervention aims to incorporate a community care pathway for liver fibrosis screening into routine care for T2D. The study protocol (Version 6, 9th Feb 2022) includes in-depth phenotyping of participants including demographic details, metabolic co-morbidities, anthropometric measurements, alcohol consumption, smoking status, current medications and average daily physical activity. During a single assessment, liver steatosis and stiffness are measured using an EchoSens FibroScan Mini+ 430. The patient record is interrogated for the most recent haematological and biochemical parameters, lipid profile, and abdominal radiology. Patients are also asked for consent to collect health care usage data from a national Government agency, Services Australia. These data will be used to determine longitudinal health outcomes and facilitate an accurate and thorough analysis of health care usage and economic costs.

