### Design and setting

This clinical trial examines the implementation of a diagnostic and risk stratification pathway for NAFLD in people with T2D. Sequential participants will be recruited to the NAFLD-RRR pathway and followed for up to 10 years to monitor their health outcomes. The detection of patients with NAFLD ± advanced fibrosis and the surveillance for HCC among “high-risk” patients will be compared to patients receiving “usual care”.

Due to the high prevalence of NAFLD and advanced fibrosis in people with T2D, it is not appropriate to conduct a randomized study of screening and risk stratification versus no intervention. All people attending the community diabetes clinics will be offered participation in the study. Study outcomes will be compared to a cohort who received “usual care” at the community diabetes clinics in the 12-months prior to implementation of the NAFLD-RRR pathway. The medical records of “usual care” patients will be audited to determine the number of people with a recorded diagnosis of NAFLD, whether an assessment of liver disease severity was performed, and the number of people referred to a liver clinic.

The study will be conducted in 3 “Beacon” diabetes clinics in the Metro South hospital and health services district (HHS), where people who are referred by their GP for specialist management of T2D are offered specialised care in a primary care setting. The Beacon model for people with complex T2D is delivered through community-based general practices where GPs with a special interest (GPwSIs) and advanced training in diabetes work alongside an endocrinologist and diabetes nurse educator [28]. The model is an alternative to standard hospital outpatient review and is fully integrated, with primary care providers and specialists co-located to provide effective, cost-efficient and patient-centred care [29]. In this model the GPwSIs take their enhanced skills back to their routine practice, so they become a referral point and source of knowledge for colleagues, potentially reducing referrals to specialist clinics. Prior to developing and implementing the NAFLD-RRR pathway, diabetes clinic/community clinicians (*n* = 24) were invited to participate in focus group discussions to obtain information about preferences and strategies for learning, support and communication [30].

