#### Secondary outcomes

***Rate of referral of “high-risk” NAFLD to Hepatology***. This will be calculated based on the number of “high-risk” patients referred to Hepatology clinics.***Rate of referral of “low-risk” NAFLD to Hepatology.*** This will be calculated based on the number of participants who receive a diagnosis of NAFLD without clinically significant fibrosis (LSM < 8.0 kPa), and the number of these “low-risk” patients that are referred to Hepatology clinics.***Rate of surveillance for HCC among “high-risk” patients.*** This will be calculated based on the number of participants with cirrhosis who are referred for surveillance for HCC according to guidelines (with liver imaging, usually ultrasound, every 6 months).***Collection of evidence about the economic benefits of a NAFLD detection/risk stratification pathway in people with T2D.*** Costs associated with the new pathway will be collected by the research team using published costing methods. Modelling will permit estimation of an incremental cost per appropriate referral via the pathway versus usual care that can be considered in light of undesirable consequences, including those associated with delayed detection and referral. Diagnostic performance of the pathway in identifying cases of advanced fibrosis will be compared with usual care.***Longitudinal outcome data.*** Participant outcome data will be collected at 12 months, 5 years and 10 years post recruitment. Linkage to Hospital Admitted Patient Data, Emergency Department data, Cancer Registry, and Death Registration will be performed by the Queensland Health Data Linkage Team for all participants. Data items will include: 1) details about hospital admissions and emergency presentations: dates, primary/other diagnosis, procedures and use of hospital-based allied health services and hospital-based clinical costings; 2) cancer (any type): date of diagnosis, site, morphology, differentiation, basis of diagnosis; 3) date and cause of death.***Development of procedures and referral pathways to facilitate patient access to required services.*** The study clinician will develop resources for the service (GP template letters). Knowledge and attitudes of clinic/community clinicians will be surveyed post-implementation of the pathway (at 2 years).***Collection of usual care data.*** Usual care data will be collected retrospectively from the three study sites for the year prior to recruitment commencement. Eligibility and exclusion criteria of controls will be the same as the intervention group except for patient consent (we will seek a waiver of consent to collect available data from patient medical records). The data collected for this usual care group will include demographic information, anthropometric measurements (height, weight, BMI, waist circumference), relevant metabolic co-morbidities, diabetes medications, and whether there is a record of alcohol consumption, a diagnosis of NAFLD and management of NAFLD – including risk stratification, blood tests, simple fibrosis scores, radiological investigations and/or referral to liver clinics.

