#### Data analysis

Differences in the proportion of patients diagnosed with NAFLD (Aim 1), identified to have advanced fibrosis/cirrhosis (Aim 2), referred to Hepatology (Aim 3), and enrolled in a surveillance program for HCC (Aim 4) before and after implementation of the intervention will be assessed using statistical tests for categorical data (e.g. Pearson’s chi-squared test, McNemar test). Where appropriate we will use regression models to identify associations between variables (eg the association between treatment group (pathway vs. usual care) and clinical and sociodemographic factors).

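### Pathway and usual care are to be compared with unadjusted tests between two non-randomised cohorts, and no case-mix adjustment of that comparison is stated

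*Protocol article*

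**What the plan says.** The Overview says the study "is a quasi-experimental study with a prospective intervention and historical control group". Design and setting rules out randomisation ("it is not appropriate to conduct a randomized study of screening and risk stratification versus no intervention") and defines the comparator: "Study outcomes will be compared to a cohort who received “usual care” at the community diabetes clinics in the 12-months prior to implementation".

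Under Secondary outcomes, in the item on usual care data, "Eligibility and exclusion criteria of controls will be the same as the intervention group except for patient consent". Control data come from medical records under a waiver and are to include "demographic information, anthropometric measurements (height, weight, BMI, waist circumference), relevant metabolic co-morbidities, diabetes medications".

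Data analysis says that differences in the proportions diagnosed with NAFLD, identified with advanced fibrosis or cirrhosis, referred to Hepatology and enrolled in HCC surveillance "will be assessed using statistical tests for categorical data". Regression is to be used where appropriate, to identify associations between variables. The single example is "the association between treatment group (pathway vs. usual care) and clinical and sociodemographic factors".

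**The concern.** With non-randomised cohorts, a crude difference in proportions mixes the effect of the pathway with any difference in the patients. The protocol gives three reasons why the patients could differ.

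- **Consent.** Pathway patients are reached by text and telephone and must agree to take part. Controls are audited without consent.
- **Period.** The controls come from the preceding year.
- **Scan success.** The per protocol analysis keeps only pathway patients who attended and could be scanned. The FibroScan section says 9–15% of examinations give no valid stiffness reading because of body habitus or skin-to-capsule depth. That filter has no counterpart in the controls, so it can create a body-size difference even if the full cohorts are alike.

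The stated tests deal with none of these. A regression of group against patient characteristics would show an imbalance, but unless it is carried into the outcome comparison the estimate stays crude. A difference in case mix could then be read as a pathway effect, or could hide one.

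**Working it through.** **1. The plan's own figure.** Sample size and statistical power assumes 20% of 240, which is 48 patients. The Wilson interval is (p + z²/2n ± z√[p(1−p)/n + z²/4n²]) / (1 + z²/n). With p = 0.20, n = 240 and z = 1.96:

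- centre = (0.2 + 0.0080)/1.0160 = 0.2047
- half-width = 1.96 × √0.000683/1.0160 = 0.0504
- interval = 15.4% to 25.5%, as stated.

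This is the precision of one proportion. It says nothing about comparability with the controls.

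**2. What each stated method can do.**

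| Method in Data analysis | Contains the outcome? | Adjusts for patient factors? |
|---|---|---|
| Pearson chi-squared | Yes | No |
| McNemar | Yes, for pairs | No; no pairing or matching of the cohorts is described |
| Regression example: group and patient factors | None named | Not as worded |

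The ITT and per protocol text and the missing-data text do not address case mix. The Discussion mentions confounding only for longitudinal health outcomes.

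**3. Size under assumed inputs.** None of the following inputs is in the protocol, which does not give the number of controls. Assume 400 per cohort, no true pathway effect, and one binary patient factor. Its share is a in the pathway cohort and b in the controls, and outcome risk is r1 with the factor and r0 without it.

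Spurious difference = (a − b)(r1 − r0).

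Example: a = 60%, b = 40%, r1 = 30%, r0 = 10%.

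- Pathway: 0.6 × 30 + 0.4 × 10 = 22%. Controls: 0.4 × 30 + 0.6 × 10 = 18%. Difference: 4 points.
- Pooled SE = √(0.20 × 0.80 × 2/400) = 0.0283. Unpooled SE = √[(0.22 × 0.78 + 0.18 × 0.82)/400] = 0.0282.
- Chance that the two-sided 5% test rejects in the pathway's favour = Φ[(0.04 − 1.96 × 0.0283)/0.0282] = Φ(−0.55) ≈ 29%. The nominal figure in that direction is 2.5%.

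Spurious difference, and chance of rejecting in the pathway's favour:

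| Share a / b | Risk 15% / 5% | Risk 30% / 10% | Risk 70% / 40% |
|---|---|---|---|
| 60% / 50% | 1 point, 7% | 2 points, 10% | 3 points, 14% |
| 60% / 40% | 2 points, 15% | 4 points, 29% | 6 points, 40% |
| 70% / 40% | 3 points, 28% | 6 points, 55% | 9 points, 73% |

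**4. Set against the planned fibrosis contrast.** The protocol sets 20% of NAFLD patients against a historical rate below 5%. Over the whole cohort the pathway figure is 48/400 = 12%.

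- Suppose usual care detects 5%. For one binary factor to lift this to 12% with no true effect, even if every detection fell in patients with the factor, its share would have to be 12/5 = 2.4 times as high in the pathway cohort. For 20% against 5% the ratio is 4.
- A milder assumed case: usual-care detection is 9% with BMI ≥35 and 4% below it, and the share with BMI ≥35 is 40% in the pathway cohort and 25% in controls. Crude usual care is 0.25 × 9 + 0.75 × 4 = 5.25% (slightly above the protocol's historical rate). With the pathway's case mix it is 0.40 × 9 + 0.60 × 4 = 6.0%.
- The bias is 0.75 points, or 0.75/(12 − 5.25) = 11% of the contrast. With 400 per cohort, z falls from 0.0675/0.0199 = 3.4 to 0.06/0.0202 = 3.0, and the conclusion stands.

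**The case against.** The article leaves room for more. The tests and the regression are given as examples, regression is to be used where appropriate, and the regression example names no dependent variable. Covariate lists and weighting schemes often sit in an analysis plan, and neither that plan nor the full protocol is shown. This part stands: a reader might infer that the effect will be estimated only by crude tests and that adjustment is excluded, and the text does not support that. What remains is that the article does name the method for Aims 1 to 4, that the method is unadjusted, and that regression is given another purpose.

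The design also limits imbalance. Controls come from the same three clinics in the year just before, under the same criteria apart from consent, and everyone attending is offered participation. The protocol contains no evidence that the cohorts differ. This lowers the likely size of the problem, but selection by consent and the difference in period remain.

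A reader might also infer that case mix could overturn the fibrosis finding, or that the referral and surveillance contrasts are only a few points and therefore fragile. The first is unlikely on the arithmetic above. The second has no basis, because the protocol gives no expected referral or surveillance rates.

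Finally, weighting whole cohorts does not make the high-risk, low-risk or cirrhosis subgroups comparable, because membership depends on whether disease was detected. That is correct, and it limits the remedy.

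**Conclusion.** The point holds in this form: the stated comparison for Aims 1 to 4 is unadjusted although the cohorts are non-randomised, come from different periods and differ by consent. No case-mix adjustment of it is stated, and the regression example describes imbalance without, as worded, adjusting the effect.

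The size rests wholly on assumed inputs: 1 to 9 points of spurious difference in the scenarios shown, with 400 per cohort and one binary factor. For the primary detection outcomes the effect is probably modest given the planned contrast of 20% versus below 5%. For referral and HCC surveillance the protocol gives no basis for a size. The change is worth making because it is cheap and gives a more credible estimate; the documents do not show that the planned conclusion would be wrong.

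**What to change.** For the proportions with all cohort members as denominator (NAFLD diagnosed, significant fibrosis identified, referred to Hepatology), state that the main estimate is an adjusted risk difference, pathway minus usual care, with 95% CI. Prespecify a short covariate set recorded in both cohorts: age, sex, BMI and diabetes medications. BMI is named for the controls; for the pathway cohort it falls under the anthropometric measurements in the Overview.

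Either of two methods would serve:

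- propensity weighting of controls to the pathway case mix, for which the regression already named is in form the propensity model; or
- an outcome regression with cohort as exposure, standardised to the pathway case mix.

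At 5% detection in an assumed 400 controls there would be about 20 fibrosis events. That favours weighting, or a very small outcome model. Keep the crude chi-squared test as supporting, and label the group-against-factors analysis as a description of balance unless it supplies the weights.

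Report referral and HCC surveillance rates within the high-risk, low-risk and cirrhosis subgroups descriptively or with explicit caution. Show them beside the overall referral proportion, because H3 expects referrals to rise in one subgroup and fall in the other.

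The cost is a few sentences and modest extra analysis, with no new data items. Audited records without BMI will need a stated handling rule. Adjustment will not remove secular trend or unmeasured selection by consent, and the report should say so.

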#### Per protocol definition

We will use an intention-to-treat (ITT) approach meaning that participants will be analysed according to their recruitment, regardless of whether they followed the model of care [40].

In a sensitivity analysis we will use a per protocol (PP) analysis by only including patients that attended their FibroScan appointment and were able to be scanned. The per protocol analysis will be applied to the primary and secondary outcomes, and the economic analysis.

An intention-to-treat approach gives an indication of the value of the model of care in practice, because it includes the missed appointments that will happen in other clinics. A per protocol approach gives an indication of the potential benefits of the model of care. If the PP results show a larger benefit than the ITT results, then it provides impetus for finding ways to help patients attend their FibroScan appointment.

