### Intervention

#### FibroScan

Transient elastography (using FibroScan) has been extensively evaluated; a liver stiffness threshold of 6.5–7.9 kPa has approximately 90% sensitivity in excluding advanced (stage 3–4) fibrosis, whereas LSM > 12–15 kPa is typically present with cirrhosis [31–35]. Transient elastography will be performed by a trained clinician as a point-of-care test, concurrently with the diabetes clinic appointment or when the participant attends for a scheduled blood test, making it easier for participants to have the test performed.

To obtain accurate results from the FibroScan assessment participants will be advised to fast for 3 h before the scheduled time of examination. Clear guidance will be provided to participants regarding fasting and withholding of T2D medications. If the FibroScan appointment is prior to 10 am, participants will be advised to fast overnight and withhold T2D medications until after the examination. If the FibroScan appointment is 10 am or later, participants will be advised to have an early breakfast, and to take their usual T2D medications, and then to fast for 3 h prior to the scan. Participants will be advised to bring a snack and all medications to clinic so that as soon as the FibroScan is completed, they can eat and take their T2D medications as required.

In around 9–15% of examinations, a valid LSM cannot be obtained because a participant’s body habitus or skin to liver capsule depth prevents an accurate assessment [8, 36]. Should this occur, the need for further review of these participants will be determined by the diabetes and study clinicians based on the history, blood tests and imaging available.

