
### Statistical analysis

#### Sample size and statistical power

We aim to recruit at least 400 patients with T2D, anticipating ~ 60% to have NAFLD (*n* = 240). If 20% of these have advanced fibrosis [8] then the 95% confidence interval will be 15.4 to 25.5%. This will provide sufficient confidence that the observed rate using the pathway differs substantially from historical detection rates of < 5% [39].

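### The per-protocol economic analysis also drops attended-but-failed scans, so its gap from intention-to-treat cannot be read as an effect of attendance

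*Protocol article*

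**What the plan says.** All of the following is in the Protocol article.

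- **Per protocol definition.** ITT by recruitment is the main approach and keeps missed appointments in. PP is a sensitivity analysis restricted to those who attended and in whom the scan could be done. Its scope is wide: "The per protocol analysis will be applied to the primary and secondary outcomes, and the economic analysis". PP is described as showing what the model could achieve, and a larger PP benefit is to be taken as a reason to help patients attend.
- **FibroScan.** In about 9–15% of examinations "a valid LSM cannot be obtained because a participant’s body habitus or skin to liver capsule depth prevents an accurate assessment". For these people, "the need for further review of these participants will be determined by the diabetes and study clinicians", using the clinical information already on hand.
- **Primary outcomes.** A NAFLD case on the pathway needs a CAP score of at least 248 dB, and a significant-fibrosis case needs an LSM of at least 8.0 kPa. Both come from the scan.
- **Secondary outcomes.** The economic ratio named is a cost per referral: "Modelling will permit estimation of an incremental cost per appropriate referral via the pathway versus usual care".
- **Resource use and costs.** Costing is from the healthcare funder's perspective. The section does not say whether an unused slot is costed, or how a failed attempt is treated in the PP analysis.

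**The concern.** The PP exclusion merges two groups. Non-attenders might have been scanned had they come. People with a failed scan did come, used operator time and possibly clinician review, and could not be measured for anatomical reasons. The plan's reading of the PP–ITT contrast, as a prompt to raise attendance, fits only the first group.

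For clinical outcomes this blurs an interpretation. For costs it goes further, because a failed attempt is part of what the pathway costs to run. Removing those people takes out cost while every scan-defined case stays in. A cost per case among the scanned is then not a level that any clinic could reach by improving attendance, yet the plan's wording would present it as the pathway's potential. The article says its findings should help guide funding decisions, so the meaning of the optimistic figure should be clear.

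**Working it through.** **1. Inputs, and the plan's own figure.** Sample size and statistical power states "We aim to recruit at least 400 patients with T2D, anticipating ~ 60% to have NAFLD", giving 240, of whom 20% have advanced fibrosis, giving 48. The article then says "then the 95% confidence interval will be 15.4 to 25.5" (percent). With p = 48/240 = 0.20, n = 240 and z = 1.96, the Wilson interval is

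- centre: (p + z²/2n)/(1 + z²/n) = (0.2000 + 0.0080)/1.0160 = 0.2047
- half-width: z·√(p(1−p)/n + z²/4n²)/(1 + z²/n) = 0.0504

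This gives 15.4% to 25.5%, so the figure is reproduced. The article gives no economic figure to reproduce.

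Other inputs: failed-scan share f = 9% to 15% (FibroScan section). Yield y among scanned patients is 0.60 for NAFLD and 48/400 = 0.12 for high risk, with the planned advanced-fibrosis count standing in for LSM ≥ 8.0 kPa.

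Assumptions not in the document: each attempted scan costs 1 unit whether or not it succeeds, and a failed examination yields neither a CAP nor an LSM case.

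**2. Cost per scan-defined case, failed scans only.**

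- ITT: 1/[(1−f)·y]
- PP: 1/y
- PP/ITT = 1 − f, which does not depend on y

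| f | Scanned of 400 | ITT per NAFLD case | PP | ITT per high-risk case | PP | PP/ITT |
|---|---|---|---|---|---|---|
| 9% | 364 | 1.83 | 1.67 | 9.16 | 8.33 | 0.91 |
| 15% | 340 | 1.96 | 1.67 | 9.80 | 8.33 | 0.85 |

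**3. Adding missed appointments (assumed).** Let a share m miss the appointment, each unused slot costing k units. With k = 0, the ratio stays at 1 − f. With k = 1, it becomes (1−m)(1−f):

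- m = 10%: 0.90 × 0.91 = 0.82 and 0.90 × 0.85 = 0.77
- m = 20%: 0.80 × 0.91 = 0.73 and 0.80 × 0.85 = 0.68

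**4. What the contrast mixes.** Take m = 10% and k = 1, and cost per high-risk case. At f = 9%, ITT is 10.18, attenders only 9.16, PP 8.33. The step due to attendance is 10.18 − 9.16 = 1.02, and the step due to failed scans is 9.16 − 8.33 = 0.83. At f = 15%, the figures are 10.89, 9.80 and 8.33, with steps of 1.09 and 1.47. If unused slots cost nothing, the whole gap comes from failed scans.

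**5. Cost per referral.** Let a share r of failed scans be referred after review, with extra review cost w per failed scan, and count all these referrals as appropriate. Leaving usual care aside,

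PP/ITT = [(1−f) + f·r/y]/(1 + f·w), which equals 1 when r = y(1 + w).

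With y = 0.12 the break-even r is 12% (w = 0), 18% (w = 0.5) or 24% (w = 1). Two examples at f = 15%:

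- w = 1, r = 0: 0.85/1.15 = 0.74, so PP is below ITT
- w = 0, r = 24%: 0.85 + 0.15 × 2 = 1.15, so PP is above ITT (8.33 against 7.25)

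**6. Incremental form with no fallback referrals.** With a usual-care referral rate e and no incremental usual-care cost, PP/ITT = [(1−f)y − e]/(y − e). The article gives no usual-care referral rate, so e = 0, 3% and 5% are assumed. The ratios are 0.91–0.85, 0.88–0.80 and 0.85–0.74 (f = 9% to 15%).

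**The case against.** A reader might infer that the PP economic figure is too low by construction. The documents do not support that for the ratio they name. Unscannable patients go to clinician review and may be referred without an LSM, so PP can lose referrals as well as costs (step 5). The review cannot be charged as a cost while being allowed no yield. The reverse reading is not secured either: high risk is defined by LSM ≥ 8.0 kPa, so if only high-risk referrals count as appropriate, unscanned people supply none and PP falls below ITT. The article does not define an appropriate referral, so the direction stays open.

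A reader might also quote an understatement of 18–24%. That needs a 10% no-show rate and every unused slot charged in full, neither of which is in the article. Nor should 48 cases be held fixed while fewer are scanned, because that count presupposes that all 400 have a result.

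The strongest general objection is that ITT is the main analysis, already carries everyone recruited, and PP is openly labelled a sensitivity analysis. This stands: no main economic estimate is biased, and nothing says the PP cost figure would decide funding. It is also fair that an article may leave costing detail to a fuller plan. Neither answers the narrower point: the article itself fixes the PP set, extends it to economics, and attaches an attendance reading that the set cannot carry.

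**Conclusion.** The point holds in a limited form. The PP set mixes avoidable non-attendance with scan failure that better attendance cannot cure, so the economic PP–ITT gap cannot be credited to attendance, whichever ratio is used.

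For cost per CAP- or LSM-defined case, PP is about 9–15% below ITT from failed scans alone. This rests on a failed attempt costing about as much as a successful one and yielding no scan-defined case. Missed appointments add to the gap only if unused slots are costed. For cost per appropriate referral PP may lie below or above ITT, depending on how fallback referrals are counted and how often they occur. The consequence is confined to a stated sensitivity result and how it is read.

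**What to change.** Amend the Per protocol definition section as follows.

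- In the economic sensitivity analysis, exclude only non-attenders, or vary the attendance rate in the cost model. Keep everyone who attended but could not be scanned, with the cost of the attempt, the cost of the fallback review and any resulting referrals.
- State that economic conclusions rest on ITT.
- Label any figure restricted to scanned patients as cost among successfully scanned patients, and do not describe it as what better attendance could achieve.

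This takes a few sentences and no new data. The downside is that, for cost per detected case, the optimistic figure becomes slightly less favourable: at the planned yield, 9.16 to 9.80 scan units per high-risk case in place of 8.33.

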### Participant outcomes

#### Primary outcomes

***Detection and documentation of NAFLD in people with T2D.*** A diagnosis of NAFLD will be made following a participant’s FibroScan with a CAP score ≥ 248 dB, with documentation in a letter to the patient’s GP and Diabetes Specialist.***Detection and documentation of significant liver fibrosis in people with T2D.*** This will be calculated based on the number of participants who receive a diagnosis of significant fibrosis (LSM ≥8.0 kPa), with documentation in a letter to the patient’s GP and Diabetes Specialist.

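### For the two scan-defined primary outcomes, a per-protocol rate above the ITT rate is built in and would occur even with perfect attendance, so it should not be read as an attendance problem

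*Protocol article*

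**What the plan says.** Under Per protocol definition, the main analysis is ITT: "participants will be analysed according to their recruitment, regardless of whether they followed the model of care". Its stated merit is that it reflects practice "because it includes the missed appointments that will happen in other clinics". The sensitivity analysis is per protocol, "only including patients that attended their FibroScan appointment and were able to be scanned", and its scope is wide: "The per protocol analysis will be applied to the primary and secondary outcomes, and the economic analysis". The section then interprets a difference between the two: "If the PP results show a larger benefit than the ITT results, then it provides impetus for finding ways to help patients attend" the FibroScan visit.

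Under Primary outcomes, the first outcome reads: "A diagnosis of NAFLD will be made following a participant’s FibroScan with a CAP score ≥ 248 dB". The second is a liver stiffness measurement (LSM) of at least 8.0 kPa. Under FibroScan, the article puts the failure rate at roughly 9–15% and gives the reason: "a valid LSM cannot be obtained because a participant’s body habitus or skin to liver capsule depth prevents an accurate assessment". The diabetes and study clinicians then decide on further review from other data.

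On who enters each group, Exclusion criteria removes people unable to consent from the pathway group. For usual care, Secondary outcomes says: "Eligibility and exclusion criteria of controls will be the same as the intervention group except for patient consent", with a waiver of consent to be sought.

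**The concern.** A comparison of PP with ITT informs about attendance only if non-attendance is what separates the two sets. Here a second filter, whether the attender could be scanned, works in the same direction and has nothing to do with turning up. The outcome itself also requires a scan. So for detection the sign of the difference follows from the definitions, and the printed reading would assign to missed appointments a loss that is partly, or even wholly, a limit of the examination. A service acting on that reading could spend effort on reminders and rebooking that cannot recover the loss.

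A related point touches the main comparison. ITT is offered as the value of the pathway in practice, but it begins at recruitment. Patients who are approached and decline are outside it, while the usual-care cohort is drawn from records without a consent step. The two groups are therefore not filtered alike.

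**Working it through.** **The plan's own figure.** The article gives no PP or ITT rate. Its only numerical target is the interval for 20% advanced fibrosis among 240 patients with NAFLD. For 48/240 the Wilson score interval is 15.43% to 25.52%, which reproduces the stated 15.4 to 25.5%. That figure is sound and is not at issue. It supplies planning rates: 60% with NAFLD, and 48/400 = 12% of all recruits with advanced fibrosis.

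**Inputs.**
- N = 400 recruits (Sample size and statistical power).
- Scan failure f = 9% to 15% (FibroScan). This is stated for LSM; I assume that such a participant also counts as not able to be scanned for the steatosis outcome.
- Detection among those scanned: 60% NAFLD, 12% fibrosis. The planning rates are assumed to apply to the scanned group.
- Missed appointments m: not given; 0% and, as an assumption, 10%.
- Uptake among those offered c: not given; 80% and 50% as assumptions.

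**Step 1, the relation.** Let x be the number detected, all of them scanned, and s = (1 − m)(1 − f) the scanned share of recruits. If unscanned recruits count as not detected:
- PP = x/(sN) and ITT = x/N = s × PP
- PP/ITT = 1/s
- PP − ITT = PP × (1 − s) = PP × f + PP × m(1 − f)

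The first term of the gap is scan failure, the second non-attendance. The usual-care rate is the same in both contrasts, so it does not alter the sign.

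**Step 2, perfect attendance (m = 0).**

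| f | PP/ITT | NAFLD: PP, ITT | Gap | Fibrosis: PP, ITT |
|---|---|---|---|---|
| 9% | 1/0.91 = 1.10 | 60%, 54.6% | 5.4 points | 12%, 10.9% |
| 15% | 1/0.85 = 1.18 | 60%, 51.0% | 9.0 points | 12%, 10.2% |

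The attendance reading would be prompted although nobody missed an appointment.

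**Step 3, 10% missed (assumption), NAFLD.**
- f = 9%: s = 0.90 × 0.91 = 0.819; ITT 49.1%; gap 10.9 points = 5.4 (scan failure) + 5.5 (non-attendance). Scan failure is about 50% of the gap.
- f = 15%: s = 0.90 × 0.85 = 0.765; ITT 45.9%; gap 14.1 points = 9.0 + 5.1. Scan failure is about 64% of the gap.

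**Step 4, if ITT counted differently.** If diagnoses by another route were counted among the unscanned at rate u, then ITT = s × PP + (1 − s) × u, which reaches PP only if u is at least PP, here 60%. With u = 5% (assumption) and full attendance, ITT is 55.1% (f = 9%) or 51.8% (f = 15%), still below 60%. If unscanned recruits were instead dropped as missing, ITT would equal PP.

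**Step 5, decliners.** Counting decliners as not detected by the pathway, detection per person offered is c × ITT. With m = 0 and ITT of 54.6% to 51.0% (f = 9% to 15%):
- c = 80%: 43.7% to 40.8%
- c = 50%: 27.3% to 25.5%

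**The case against.** The sentence is softly worded and belongs to a labelled sensitivity analysis. No test or threshold hangs on it, and the article openly presents PP as potential benefit, so a higher PP value is expected. Conditioning on a completed scan is a legitimate way to show that potential. The Missing data section also promises to investigate any variable with more than 5% missing, which the expected 9–15% would trigger. All of this is fair. It limits the weight of the point but does not correct an interpretation that names attendance alone.

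Three stronger readings are tempting and are not supported.
- **That PP must exceed ITT in every case and for every outcome.** The article implies, but does not state, that unscanned recruits count as not detected; under other handling the inequality is only very likely, or becomes an equality. The PP analysis also covers secondary and economic outcomes. Referral rates among high-risk or low-risk patients have scanned patients as their denominator, so PP and ITT coincide. Low-risk referrals as a share of all participants would look worse in PP. Costs can move either way.
- **That the comparison carries no information.** Only its sign is uninformative for detection. Its size, split by cause, shows how much is lost to missed visits.
- **That the ITT rate is shown to overstate the pathway's yield in a clinic.** Declining a research study is not the same as declining a routine scan, so counting every decliner as undetected gives a lower bound. Uptake is not stated, and the controls still face the same criteria apart from consent.

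**Conclusion.** The point holds for the two primary detection outcomes. With unscanned recruits counted as not detected, PP exceeds ITT whenever anyone is unscanned and a case is found; at the article's own failure rate that is practically certain. At full attendance the ratio is 1.10 to 1.18, with a gap of 5.4 to 9.0 points for NAFLD if 60% of those scanned are positive. At an assumed 10% missed, roughly half to two thirds of the gap would still remain if everyone attended. The printed inference would therefore mislead. It does not invalidate the ITT analysis.

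The consent asymmetry is real and does bear on the main contrast, but its size cannot be derived from the article. The figures for decliners rest on assumed uptake and bound the yield from below.

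**What to change.** 1. Replace the inference sentence. Report attendance among recruits and valid scans among attenders as two separate rates, and attribute to attendance only the non-attendance part of the PP–ITT gap.
2. State that in the ITT analysis of the primary outcomes unscanned recruits count as not detected by the pathway. Beside the existing PP set, add an analysis of all attenders in which those who could not be scanned are kept and counted as not detected. Comparing it with ITT isolates attendance; comparing it with PP isolates scan failure.
3. From the appointment databases that are already prescreened, report numbers eligible, offered and declining. Give detection per all eligible patients as a supporting estimate, labelled as a lower bound.

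Cost: a few sentences and aggregate counts, with no new patient-level data. The drawbacks are a lower supporting rate beside the headline, and possibly a note to the ethics committee about aggregate counts of decliners.
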